Rate of complete margin clearance in patients with malignant tumours	a. Microscopically complete margin clearance > 0.1 cm margin clearance, R0 (CRM−). b. Microscopic margin clearance ≤ 0.1 cm, R0 (CRM+). c. Microscopic margin involvement (R1) resections according to the 8th edition of the UICC TNM classification.
Lymph nodes in patients with malignant tumours	a. Number of lymph nodes resected. b. Number of tumour-positive lymph nodes.
Postoperative outcomes	
Mortality (%)	From the day of surgery until postoperative day 90.
Quality of recovery	Measured via the quality of recovery questionnaire QoR-15 [28], assessed at baseline and on POD 4.
Time to functional recovery (days)	Up to postoperative day 90; defined as: independently mobile at the preoperative level, sufficient pain control with oral medication alone, ability to maintain sufficient (i.e. > 50%) daily required caloric intake by mouth, no intravenous fluid administration and no signs of infection [29].
Total length of intensive care unit stay (days)	From the day of index operation up to postoperative day 90.
Length of hospital stay (days)	From the day of index operation up to the day of discharge.
Rate of superficial and deep surgical site infections (SSIs)	As defined by the Centres of Disease Control and Prevention (CDC) within 30 days [30]. Organ-space SSIs are excluded from this measurement as they are independent of surgical access, but rather depend on the underlying surgery. Consequently, organ-space SSIs will be recorded in the overall complication rate if applicable.
Pancreas-specific complications	Rate and severity within 90 days of: a. Postoperative pancreatic fistula as defined by the ISGPS [31]. b. Postpancreatectomy haemorrhage as defined by the ISGPS [32]. c. Delayed gastric emptying as defined by the ISGPS [33]. d. Biliary leak as defined by the ISGLS [34]. e. Chyle leak/lymphatic fistula as defined by the ISGPS [35].
Non-surgical re-interventions	Number of non-surgical re-interventions within 90 days after PD (e.g. image-guided drain placement, angiography with stenting/other interventions, endoscopy).
Re-operations	Number of re-operations within 90 days after PD.
Hospital re-admissions	Number of hospital re-admissions within 90 days after PD.
Pain	Pain scores at rest and during movement according to the Numeric Rating Scale (NRS) on POD 2 and 4.
Health-related quality of life (HRQoL)	Measured by the SF-36 at baseline, 30 and 90 days after index operation [36].

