### Description of trial visits

During the screening visit (1–14 days before surgery), inclusion and exclusion criteria are assessed (Table 2). After the patient has given informed consent, the demographic and baseline data, the ASA score, the updated Charlson Comorbidity Index [37], the health-related quality of life as measured by SF-36 [36], the quality of recovery as established using questionnaire QoR-15 [28] and the pancreas-specific medical history (indication for surgery, pre-existing diabetes mellitus, pre-existing exocrine insufficiency, neoadjuvant treatment, preoperative cholestasis, preoperative biliary drainage) are assessed and documented. Visit 2, including assessment of intraoperative and perioperative parameters as well as serious intraoperative complications, takes place on the day of surgery. Also documented during visit 2 are the type of pancreatic resection, extent of lymphadenectomy, additional organ resections, texture of the pancreas, size of the pancreatic duct at the transection site and drain insertion. Four inpatient follow-up visits on postoperative days (POD) 4, 8 and 12 and the day of discharge will be performed in person, and two telephone follow-up visits 30 and 90 days after surgery will be conducted to evaluate the primary and secondary outcome parameters (see Table 1). If a patient is discharged before POD 12, visit 5 can be omitted.

**Table 2 Tab2:** Trial visits

Visit	1	2	3	4	5	6	7	8
	1–14 days before surgery	Day of surgery (day 0)	POD 4	POD 8	POD 12	Day of hospital discharge	POD 30	POD 90
	Outpatient/inpatient	Inpatient					Inpatient/telephone	
Eligibility criteria	X							
Informed consent	X							
Baseline demographics and clinical data	X							
Randomisation	X							
Quality of life questionnaire (SF-36)	X						X	X
Quality of recovery (QoR-15)	X		X					
Intervention		X						
Serious intraoperative complications		X						
Intraoperative secondary endpoints (e.g. operation time, blood loss, conversion rate, resection status)		X						
Surgeon’s mental workload/stress		X						
Assessment of primary endpoint (CCI)			X	X	X	X	X	X
Postoperative secondary endpoints (e.g. re-interventions, pain, time to functional recovery)			X*	X	X	X	X	X
Procedure-related costs, all inpatient hospital costs								X

*POD* postoperative day

*Pain needs to be assessed on POD 2 and 4

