### Statistics

#### Sample size calculation

Given that EUROPA is an exploratory trial, no formal sample size calculation was performed. However, a clinically relevant mean difference for the CCI is 10 [25, 26] while the mean standard deviation is approximately 20 in major abdominal surgery [38]. Including 64 patients (32 per group) in the analysis, this effect size could be estimated with a 95% confidence interval (CI) of [3.07, 16.93]. Considering that approximately eight patients per group will undergo neither RPD nor OPD due to inoperability or indication for another type of surgery (ascertained during the exploratory stage of the operation), a total of 80 patients will need to be allocated to the trial (Fig. 1).

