#### Analysis variables and statistical methods

The primary endpoint is the CCI within 90 days after the intervention. As a primary result, the 95% CI for the difference in the means between the two groups will be reported. Since the CCI is approximately normally distributed [25], the 95% CI can be computed by means of the normal distribution. Further descriptive measures are reported in terms of mean and standard deviation.

Data analysis will be based on three analysis sets. The intention-to-treat (ITT) set comprises all patients in the group to which they were randomised (converted patients remain in the RPD group) and serves as the primary analysis set. Patients that receive an operation other than PD or total pancreatectomy (explorative laparotomy, diagnostic laparoscopy, etc.) are excluded from further analysis and proceed directly to the end-of-study visit (V8). The per-protocol (PP) set consists of all patients treated per protocol without major protocol violation and without conversions. No missing data will be imputed in the PP set. In addition, the as-treated set will be analysed, which considers the patients in the group in which they were finally treated (i.e. converted patients in the OPD group). There is no evidence that the converted patients will have a higher postoperative CCI than those patients randomised to and remaining in the OPD group. Therefore, and due to the exploratory character of this trial, the as-treated set is an important complement to the ITT and PP sets in this trial.

The primary endpoint is expected to be missing for a small number of patients, since it is objective and short term. In these cases, the primary endpoint is imputed using mean imputation based on the treatment group. As sensitivity analyses, worst-case and best-case scenarios are investigated. Missing values of the primary endpoint will be imputed using the lowest and the highest value of the corresponding treatment group.

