The secondary endpoints are described as mean values along with standard deviations, median values, quartiles, minimum and maximum for continuous endpoints, and relative and absolute frequencies for categorical endpoints, stratified for treatment groups. Effect sizes (mean difference for continuous data, Hodges–Lehman estimator for scores and risk difference for binary data) including 95% CIs will be reported. The safety analysis includes calculation of frequencies and rates of both minor (Clavien–Dindo class I and II) and major complications (Clavien–Dindo class III to V) together with 95% CIs. Statistical methods will be used to assess the quality of data and the homogeneity of the intervention groups.

Details of statistical analyses as well as the handling of potential data problems will be defined in a statistical analysis plan (SAP) prior to database closure.

All analyses are exploratory, having only descriptive character, and will be conducted using SAS version 9.4 or higher.

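### The estimator named for scores makes no use of the baseline SF-36 and QoR-15 values as usually computed, which costs precision but causes no bias

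*Protocol article*

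**What the plan says.** Under Analysis variables and statistical methods, the Protocol article fixes the effect measures for secondary endpoints: "Effect sizes (mean difference for continuous data, Hodges–Lehman estimator for scores and risk difference for binary data) including 95% CIs will be reported". No covariate or change from baseline is mentioned with them. For the primary endpoint, "the 95% CI for the difference in the means between the two groups will be reported".

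Table 1 defines quality of life as "Measured by the SF-36 at baseline, 30 and 90 days after index operation" and quality of recovery as a QoR-15 score "assessed at baseline and on POD 4". Table 2 places both baseline questionnaires at the screening visit. That visit also records risk factors, including the ASA score, "the updated Charlson Comorbidity Index" and the pancreas-specific history.

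The same statistics section says that homogeneity of the groups will be assessed, leaves analysis details to a SAP that is not shown, and calls all analyses exploratory and descriptive.

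**The concern.** SF-36 and QoR-15 are the two endpoints in Table 1 defined with a baseline and a follow-up measurement on the same scale. A patient's score before surgery usually predicts the score afterwards. An analysis that compares follow-up scores alone leaves that predictable part of the variation in the error term.

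The article does name an estimator for scores, so this is more than detail left to the SAP. The Hodges–Lehmann shift is the median of all between-group pairwise differences and in its usual form has no place for a covariate. If these questionnaires were instead treated as continuous, the article would give a mean difference, again with no baseline named.

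At stake is the width of the intervals for the patient-reported outcomes. With about 64 patients analysed they will be wide, and the trial is meant to inform the design of a confirmatory trial.

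**Working it through.** **Inputs.** From Sample size calculation: 64 analysed, 32 per group; for the CCI, "a clinically relevant mean difference for the CCI is 10" and "the mean standard deviation is approximately 20 in major abdominal surgery". The baseline–outcome correlation r is not in the article. It is assumed to be 0.3, 0.5 or 0.7.

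**The plan's own precision figure.** The article gives no precision for SF-36 or QoR-15, only for the CCI: "Including 64 patients (32 per group) in the analysis, this effect size could be estimated with a 95% confidence interval (CI) of [3.07, 16.93". Its half-width of 6.93 equals 1.96 × 20/√32, the form for one group. The two-group form is 1.96 × 20 × √(2/32) = 1.96 × 5.00 = 9.80, giving [0.20, 19.80]. That discrepancy is a separate matter; the two-group form is used here.

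**Unadjusted interval for a score.** In outcome SD units the half-width is 1.96 × √(2/32) = 1.96 × 0.25 = 0.49.

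**Adjusted interval.** Adjustment for the baseline score multiplies the standard error by √(1 − r²). Estimating k covariates inflates the variance on average by (n − 3)/(n − k − 3), for normal covariates. With n = 64 and k = 1 this is 61/60 = 1.017, a factor of 1.008 on the width.

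| r (assumed) | √(1 − r²) | Half-width (SD) | Narrower by | Narrower after × 1.008 | Equivalent N, 64/(1 − r²) |
|---|---|---|---|---|---|
| 0.3 | 0.954 | 0.47 | 5% | 4% | 70 |
| 0.5 | 0.866 | 0.42 | 13% | 13% | 85 |
| 0.7 | 0.714 | 0.35 | 29% | 28% | 125 |

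The last column is the number that would have to be analysed without adjustment for the same width, before the small inflation. At r = 0.1 the net factor is 0.995 × 1.008 = 1.003, so nothing is gained.

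The widths are those of a difference in means. For roughly normal scores the Hodges–Lehmann interval should be close to this; for skewed or bounded scores the comparison is approximate.

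**Change from baseline instead.** With equal SDs at both times, the change-score factor is √(2(1 − r)): 1.183, 1.000 and 0.775 at r = 0.3, 0.5 and 0.7. At 0.3 it is 18% wider than ignoring baseline, and at each r it is wider than the adjusted estimate.

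**CCI, for comparison.** There is no baseline CCI, so only the variance share R² explained by risk factors matters. Adjustment breaks even at R² = k/(n − 3): 1/61 = 0.016, 2/61 = 0.033 and 3/61 = 0.049 for one, two and three covariates. With two covariates the half-width of 9.80 becomes:
- R² = 0.05: 9.80 × √(0.95 × 61/59) = 9.71
- R² = 0.10: 9.80 × √(0.90 × 61/59) = 9.45
- R² = 0.20: 9.80 × √(0.80 × 61/59) = 8.91

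Nothing in the article indicates which R² applies.

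**The case against.** The strongest reply is that covariate adjustment is normal SAP content and the article defers details to the SAP. A mean difference can be an adjusted one, and a Hodges–Lehmann estimate can be computed on changes from baseline. This stands against a reading that no analysis in the trial will use the baseline values; the article cannot show that, and it also assigns baseline data to the homogeneity check and to subgroup analyses. It does not remove the point. The estimator named for scores ignores baseline in its usual form, and the change-score variant is the less efficient use of baseline.

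A second reply is that Hodges–Lehmann is a sound robust choice for bounded scores in a descriptive trial. That is accepted, and it is why the estimate should stay.

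A reader might also infer more than the article supports:
- **That chance imbalance biases the results.** At 32 per group, a difference above 0.5 baseline SD on a given covariate has a probability of 4.6%, and would shift an unadjusted estimate by 0.5 × r outcome SD. Over repeated randomisation such shifts average to zero, and the unadjusted interval already allows for them.
- **That the raw CCI difference is a flawed primary analysis.** The CCI has no baseline value, and any gain rests on an assumed R². Equating R² = 0.20 with 80 patients (64/0.8) ignores the cost of estimating covariates: with three, 64/(0.8 × 61/58) = 76.
- **That randomisation is unstratified.** The article describes no stratification, but a condensed article's silence does not show there is none.

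**Conclusion.** The point holds for SF-36 and QoR-15. The article names an estimator for scores that normally leaves a measured baseline unused, and a baseline-adjusted difference would be more precise at no cost in data. The interval would be about 5%, 13% or 29% narrower at correlations of 0.3, 0.5 or 0.7, less under one percentage point for estimating the covariate.

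This rests on the assumed correlations, a roughly linear relation between baseline and follow-up, and 32 patients per group with both measurements. Below a correlation of about 0.13 (√(1/61)) there is no gain. The matter is one of precision in secondary endpoints; it does not touch the validity of the randomised comparison or of the primary result.

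**What to change.** State in the SAP, before database closure, that for QoR-15 at POD 4 and each reported SF-36 score the treatment difference will be estimated by ANCOVA with the baseline score as covariate, with its 95% CI. For SF-36 this can be done separately at days 30 and 90 or in one repeated-measures model. Report the Hodges–Lehmann estimate and its interval alongside. The two need not target the same quantity when scores are skewed, so label each.

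Confirm that the baseline questionnaires are completed before the allocation is known. Table 2 puts them and randomisation in the same visit without an order, and the trial is open-label.

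Optionally, add a supplementary CCI model with one or two risk factors named in advance, next to the raw difference. Its gain is uncertain and may be nil if R² is below about 0.05. Pancreatic texture and duct size should not be used, since they are recorded on the day of surgery, after randomisation.

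The cost is a few sentences in the SAP and a few lines of code. No new data, visits or patients are needed.

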#### Data management

An eCRF will be used for data collection (attached to this protocol as supplementary material). To ensure a safe and secure environment for the data acquired, data transmission is encrypted with secure socket layer (SSL) technology. All changes to data are logged with a computerised timestamp in an audit trail. All data will be pseudonymised. To guarantee high data quality, the data validation rules will be defined in a data validation plan. The completeness, validity and plausibility of data will be checked at the time of data entry (edit checks) and by using validating programmes that will generate queries. The completed eCRF must be reviewed and signed by the investigator named in the trial protocol or by a designated sub-investigator. The investigator or the designated representative is obliged to complete the eCRF as soon as possible after information is collected and to clarify or explain the queries.

Patients and surgeons will be identified solely by means of their individual identification code. Trial-specific documents will be stored in accordance with local data protection law and GCP guidelines and will be handled in strictest confidence. For the protection of these data, organisational procedures are implemented to prevent the distribution of data to unauthorised persons.

Once no further corrections are to be made, the database will be locked. All data management procedures will be conducted according to written defined standard operating procedures that guarantee efficient conduct complying with GCP. At the end of the study, the data will be transformed into different formats (e.g. csv files) for archiving purposes and to ensure future accessibility of the data.

#### Data monitoring

Quality assurance will be carried out following a risk-based strategy in cooperation of monitoring, data management and biostatistics. Independent monitoring includes clinical on-site visits and will follow standard operating procedures to ensure compliance with the trial protocol, the principles of the Declaration of Helsinki and GCP guidelines and data protection and other relevant legal aspects.

The primary endpoint, expressed in terms of the CCI, assesses safety. Therefore, adverse events are represented by minor complications (Clavien–Dindo class I and II) and serious adverse events are represented by major complications (Clavien–Dindo class III to V).

A Data and Safety Monitoring Board (DSMB) made up of independent experts and a patient representative will monitor the progress of the trial. DSMB members will receive a written safety report every 6 months and will advise on continuation, modification or termination of the trial.

The trial may be prematurely closed by the coordinating investigator in consultation with the steering committee and the DSMB. Factors that may necessitate termination of the trial include morbidity or complications that indicate a potential health hazard caused by the study treatment or relevant external evidence.

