### Study registration, ethics and consent

The trial protocol was approved by the ethics committee of the University of Heidelberg (*Ethikkommission Medizinische Fakultät Heidelberg*; S-025/2020, 3 February 2020), and the trial was registered with the German Clinical Trial Register (DRKS), an approved primary registry in the WHO network (DRKS00020407, 9 March 2020; UTN U1111-1245-8931, 30 December 2019) before inclusion of the first patient. The trial will be conducted at the Department of General, Visceral and Transplantation Surgery, University Hospital Heidelberg, Germany, in accordance with the Good Clinical Practice (GCP) guidelines and the Declaration of Helsinki. More than 250 PDs are performed each year at the Department of General, Visceral and Transplantation Surgery, and it is certified as a centre of excellence for minimally invasive surgery by the German Society for General and Visceral Surgery (*Deutsche Gesellschaft für Allgemein- und Viszeralchirurgie*). Conservatively, five patients per month can be included in the trial. Thus, given the need to recruit 80 patients (see the “Sample size calculation” section), completion of recruitment is feasible within 18 months. The independent statistical analysis will be performed at the Institute of Medical Biometry and Informatics (IMBI) of the University of Heidelberg. All patient-related information is subject to medical confidentiality according to the European General Data Protection Regulation (*Datenschutzgrundverordnung*, DSGVO), the Federal Data Protection Act (*Bundesdatenschutzgesetz*) and the State Data Protection Act (*Landesdatenschutzgesetz*).

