### Primary and secondary endpoints

The primary endpoint of the EUROPA trial is cumulative morbidity within 90 days after PD, assessed by means of the CCI. The CCI is based on the established Clavien–Dindo classification of postoperative complications, which has gained widespread acceptance [24]. The Clavien–Dindo classification grades postoperative complications according to their sequelae, ranging from grade I (any deviation from the normal postoperative course without the need for pharmacological treatment) to grade V (death). The CCI score ranges from 0 (no complication of any kind during the postoperative course) to 100 (death of patient). The CCI permits objective assessment of cumulative postoperative morbidity even in an unblinded study setting. The CCI was developed jointly by surgeons and patients and considers the patient’s perspective as well as objective parameters of surgical effectiveness [25]. It is validated for the pancreatic surgical population and a difference of 10 is regarded as clinically relevant [26].

The secondary endpoints cover important oncological, clinical, economic and patient-relevant outcomes (Table 1).

**Table 1 Tab1:** Definition of secondary endpoints

Secondary endpoint	Definition
General outcomes	
Feasibility of recruitment	Recruitment goal of *n* = 80 patients within 18 months.
Costs (€)	Procedure-related costs and all inpatient hospital costs up to POD 90.
Intraoperative outcomes	
Duration of surgery (min)	RPD: from the start of positioning of the robot to the end of skin closure. OPD: from the beginning of skin incision to the end of skin closure.
Blood loss (ml)	As recorded in the anaesthesiology report.
Serious intraoperative complications	Any untoward medical/surgical occurrence that results in death, is life-threatening, requires prolongation of existing hospitalisation or results in persistent or significant disability/incapacity. Intraoperative in this context is defined as from the beginning of anaesthesia until the end of skin closure.
Conversion rate (%)	Conversion rate from robotic to open surgery.
Surgeon’s mental workload/stress	Self-evaluation according to the National Aeronautics and Space Administration Task Load Index [27] at the end of surgery.
Oncological outcomes	

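### The SAE definition rests on a postoperative grading scale, so a non-fatal serious intraoperative complication without a grade III to V sequela falls outside it

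*Protocol article*

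**What the plan says.** Four places in the protocol article bear on this.

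- *Data monitoring* argues that the primary endpoint, the CCI, itself assesses safety. From that it derives both event categories. Grades I and II stand for the non-serious events, and for the higher grades it says: "serious adverse events are represented by major complications (Clavien–Dindo class III to V". It gives no other route by which an event becomes an AE or SAE.
- *Primary and secondary endpoints* sets the scope of the scale: "The Clavien–Dindo classification grades postoperative complications according to their sequelae".
- Table 1 lists serious intraoperative complications as a secondary endpoint with its own criteria: "Any untoward medical/surgical occurrence that results in death, is life-threatening, requires prolongation of existing hospitalisation or results in persistent or significant disability/incapacity". The window runs from the start of anaesthesia to completed skin closure. Table 2 places this assessment at visit 2, the day of surgery. It marks CCI assessment from the POD 4 visit onward.
- *Analysis variables and statistical methods* says that the safety analysis covers minor (I and II) and major (III to V) Clavien–Dindo complications with 95% CIs. Its sentence on safety does not name intraoperative complications. The same section has all secondary endpoints described by treatment group, with risk differences and 95% CIs for binary data.

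**The concern.** The trial compares two ways of performing the same resection, so the operation is where the arms differ most directly. Safety is among the things the pilot is meant to measure, and *Interventions* allows conversion to open surgery for intraoperative or technical reasons. If the SAE category is built only on a postoperative scale, an event that threatens life during the operation and is then managed without a major postoperative complication is not counted as serious in the safety monitoring.

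What is at stake is oversight, not estimation. *Data monitoring* names morbidity or complications that signal a health hazard as grounds for closing the trial. A safety summary compiled strictly from the stated SAE definition would leave out this class of event. The same event would also be serious in one table of the final report and absent from the safety table.

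**Working it through.** This is a check of definitions, so the passages are set side by side and types of event are run through them.

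**Inputs**
- SAE: Clavien–Dindo III to V (*Data monitoring*).
- AE: Clavien–Dindo I and II (*Data monitoring*).
- Scope of the scale: postoperative complications (*Primary and secondary endpoints*).
- Serious intraoperative complication: Table 1 criteria, anaesthesia start to skin closure.
- Safety analysis: Clavien–Dindo I and II, and III to V (*Analysis variables and statistical methods*).
- Mortality: counted from the day of surgery to POD 90 (Table 1).

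**Classification under the text as written**

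| Intraoperative event meeting Table 1 | Secondary endpoint, by arm | AE or SAE in *Data monitoring* | In the safety analysis as described |
|---|---|---|---|
| Death | Yes; also in mortality | SAE (grade V is death) | Yes |
| Non-fatal, later grade III or IV sequela | Yes | SAE, through the sequela | Yes, through the sequela |
| Non-fatal, later grade I or II sequela only | Yes | Sequela is an AE; no SAE | As a minor complication only |
| Non-fatal, no postoperative complication | Yes | Neither | No |

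The first two rows are covered. The last two are the gap: the event is serious by Table 1 and not an SAE by *Data monitoring*. In the last row it is not an AE either.

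**Size**

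The article gives no expected rate of serious intraoperative complications, so the number of affected patients cannot be computed. The weight of one such patient can be. With 32 per group analysed (*Sample size calculation*), one patient is 1/32 = 3.1 percentage points of an arm's serious-event rate. With all patients allocated to an arm as the denominator (32 + 8 = 40), it is 1/40 = 2.5 points. Both figures assume that the patient has no other grade III to V complication.

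**The case against.** The strongest reply is that these events are already handled. They have an explicit definition, a fixed visit and a planned between-arm comparison with a confidence interval. Conversion is also a secondary endpoint, with reasons documented. Deaths count in mortality, and any later major sequela is an SAE. Using Clavien–Dindo grades for AEs and SAEs is a declared choice, and the article does not list what the DSMB report contains, so it does not show that intraoperative events are left out.

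Most of this stands, and it is why the point is narrow. It does not close the gap. *Data monitoring* states a definition and gives a reason for it, and that reason does not reach the intraoperative period. This is a rule as written, not a detail left to the full protocol.

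Some stronger readings are tempting but unsupported:

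- **SAEs are reported only every six months.** The text says "DSMB members will receive a written safety report every 6 months", which sets the interval of that report. It sets none for SAE reporting, and expedited notification may be in the full protocol.
- **The DSMB sees only two reports before recruitment ends.** At the planned rate ("Conservatively, five patients per month can be included in the trial"), recruitment takes 80/5 = 16 months, and reports counted from recruitment start fall at months 6 and 12. An 18-month period also has two strictly before its end. But *Trial status* gives June 2020 to some point in 2022, at least about 19 months, which adds month 18 and so gives at least three. Early closure is not tied to a report date, and a six-month interval contradicts nothing in the article.
- **A grade II complication that prolongs the stay should be an SAE because Table 1 names prolongation.** That criterion belongs to one endpoint confined to the intraoperative window. It is not a trial-wide seriousness rule.
- **The earlier minimally invasive trial that was stopped shows the danger.** It stopped for mortality, which is grade V and already an SAE here. The *Discussion* also says that it supports no valid conclusion about RPD.

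**Conclusion.** The point holds in a limited form. Non-fatal serious intraoperative complications with no grade III to V postoperative sequela meet the seriousness criteria of Table 1 but lie outside the SAE definition in *Data monitoring*. The safety-analysis sentence in *Analysis variables and statistical methods* does not name them. They are not lost, because they are collected and compared between arms as a secondary endpoint. The primary analysis and the sample size are unaffected.

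The conclusion rests on taking Clavien–Dindo as the article describes it, a grading of postoperative complications, and on no other SAE route applying. If the full protocol already counts Table 1 events as SAEs, only the article's wording needs correcting. Whether the DSMB report includes them cannot be told from the article.

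**What to change.** Reconcile the three sections as follows.

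1. In *Data monitoring*, state that SAEs comprise Clavien–Dindo III to V complications or any serious intraoperative complication as defined in Table 1.
2. In *Analysis variables and statistical methods*, add the Table 1 serious intraoperative complications to the safety analysis, with frequencies, rates and 95% CIs by arm.
3. State that the DSMB safety reports show these complications by arm, together with conversions (which, as Table 1 defines them, arise only in the robotic arm).

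The intraoperative data are already recorded at visit 2, so no new data collection, visit or change in sample size is needed. The cost is a change of wording and a slightly longer safety report.
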